**Methods/Design:**

A Realistic Evaluation (RE) design will address the questions “What works, for whom, and in what circumstances?” This study includes pre and post comparisons for a cohort of approximately 20 people taking part in IPS, and a similar number of controls, over a one year period. The RE also consists of interviews with practitioners and offenders in order to understand how IPS works and develops within the criminal justice system (CJS). By applying this framework the research can go from discovering whether IPS works, to how and why (or why not) IPS works. This is achieved by examining where the intervention is occurring (Context (C)), the mechanisms (M) that create particular behaviours, and how the outcomes (O) from the intervention all come together (CMOs). Employment outcomes will also be examined for all participants.

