### Offender interviews

Previous research indicates that the employment rate of offenders released from prison is 25 % [9]. The IPS literature consistently demonstrates that participation in IPS doubles the percentage of people in paid employment [41]. However, this excludes offenders who, for reasons cited earlier, face additional obstacles to employment. Therefore, in consideration of previous IPS research and the experience of the research team, an estimated hypothesis for the primary outcome is that 40 % of those on IPS will work at least one day in paid employment compared with 25 % for those who do not take part in IPS: at least eight of the intervention group of 20 will obtain work, as compared to five of the control group. A 15 % net increase in the competitive employment rate is both clinically and socially meaningful as not only would this reduce the range of costs to society that are associated with this population, but according to previous findings employment can have a positive impact on each individual’s life satisfaction and their mental health, especially if this is sustained [37, 38].

As there is no randomisation with regards to who takes part in IPS and who does not take part in IPS, motivation to gain employment will be measured, making it possible to control for the effect of differences in motivation on outcomes using logistic regression.

Given that the majority of recruitment and consent will be taken within prison the research team estimate that most (80 %) of those approached to participate in the research will take part. Furthermore, as not everyone who is approached will take part in the research, even though they may take part in IPS, it is believed that 36 people within each group will need to be approached.

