### Reconviction analysis

A sample of similar size matched on criteria that influence reoffending, will be compared with the study participants to determine the probability of reconviction with and without IPS involvement. This ‘reconviction analysis’ will also involve comparisons between the two groups on new index offence, sentence length, and overall circumstances.

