### Quantitative data

To determine whether there was a significant difference between those who took part in IPS and those who did not, concerning whether competitive employment was gained, a Chi-square analysis will be carried out at the six and 12 month intervals. Similarly, a logistic regression will also be carried out at these intervals in order to control for a participants’ motivation to work and assess covariates (e.g. age, gender, criminality) between both groups. Motivation to work will be controlled for during all comparisons, as the decision to seek employment is a personal choice.

Questionnaires pre and post IPS will be analysed using statistical independent sample t­tests, using a Statistical Package for the Social Science (SPSS) software, to determine whether overall significant improvements exist within mental health and social stability between those who did, and those who did not take part in IPS. A case by case examination of client yes/no responses in interviews, social stability measures (job contract and income, accommodation, social network etc.), and structured aspects within social stability questionnaires will be examined in conjunction with all other data, such as themes gained from interviews, to supplement all research questions and to make improvements and recommendations concerning IPS. Unemployment rates, jobs created data, fidelity to the IPS model and any changes in crime rates for particular areas will also be taken into account when examining results.

Descriptive data will be produced to meet the additional secondary outcomes; employment outcomes achieved. All other structured information from the relevant validated measures will be examined case by case for patterns of change amongst those who were part of IPS in comparison with those who were not part of IPS. Appropriate statistical analyses will account for any attrition variation between the IPS and no IPS control condition across the three data collection points. Missing data will also be excluded using the appropriate statistical techniques.

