By examining Police National Computer (PNC) data the proven one year re­offending rates of individuals who took part in IPS will be made clear. Specifically, whether any offence has been committed and whereby a conviction, caution, warning or reprimand was received within the one year follow up and six month waiting period [56]. This will also give an indication of the severity and regularity of reoffending in comparison to each individual’s own previous offending behaviour.

To generate stronger findings that go beyond whether an individual offends or not and how this compares to their previous offence history it is important to determine what would have happened to the participants on IPS should they not have taken part, an estimate is needed. This estimate is known as the ‘counterfactual’ [57] and will enable a comparison in reoffending rates of those who took part in IPS with those who did not. Making this comparison ensures that the only major difference in characteristics between both groups is the IPS intervention. In order to isolate the effects of IPS in this way those on IPS will be matched on key factors which influence reoffending with a comparator group (No IPS). A logistic regression, Propensity Scored Matching (PSM), will be utilised to carry out this comparison.

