## Discussion

The study will be carried out across a wide geographical area. A total of eight sites, seven prisons and one probation area are eligible to provide referrals to the study, including both people who do and do not want help to find competitive employment via the IPS service. This will therefore involve conducting research within the demands of a criminal justice setting, with a population many of whom have chaotic lifestyles.

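### The plan says the matched reconviction comparison guarantees that IPS is the only major difference between groups; propensity matching in a self-selected sample of about 20 cannot do that, so the result should be reported as an association

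*Protocol article*

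**What the plan says.** The claim is in the protocol article under Quantitative data, in the text on Police National Computer data and the counterfactual: "Making this comparison ensures that the only major difference in characteristics between both groups is the IPS intervention". The next sentences give the aim and the method: "In order to isolate the effects of IPS in this way those on IPS will be matched on key factors which influence reoffending", and "A logistic regression, Propensity Scored Matching (PSM), will be utilised to carry out this comparison". I read this as a score estimated by logistic regression and then used for matching.

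Reconviction analysis describes the comparator: "A sample of similar size matched on criteria that influence reoffending, will be compared with the study participants". The abstract gives the study size as "a cohort of approximately 20 people taking part in IPS, and a similar number of controls".

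Three other statements bear on the claim:

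- Offender interviews: "As there is no randomisation with regards to who takes part in IPS and who does not take part in IPS".
- Discussion, on referrals: "including both people who do and do not want help to find competitive employment via the IPS service".
- Quantitative data: "Motivation to work will be controlled for during all comparisons, as the decision to seek employment is a personal choice".

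Research question 5 asks for the effect of IPS on reoffending, and offending behaviour is a secondary outcome. The article gives no sample size, power or precision figure for the reconviction analysis.

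**The concern.** The article asserts a property that the named method lacks. A propensity score can balance only the variables entered into it. Here those are unnamed factors that predict reoffending. Any cause of both IPS uptake and reoffending that is outside the score remains as a difference between the groups.

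The article itself points to such a cause. Referrals include people who do and do not want help to find work. The Background reports that most offenders wish to stop offending and see employment as the way to do so. The wish to work could therefore raise IPS uptake and lower reoffending even if IPS does nothing.

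At stake is the answer to research question 5. As written, a lower reoffending rate in the IPS group would be read as the isolated effect of IPS, when self-selection could produce it.

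**Working it through.** **1. Can the claim hold for the named method?** The article describes a non-randomised study, entry that depends on wanting help, and matching on measured factors. Together these allow at most approximate balance on the factors in the score. No later sentence limits the claim to measured factors.

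**2. Does the motivation promise reach this comparison?** Table 1 lists the motivation scale as a self-administered measure for offender participants at baseline, 6 and 12 months. Two readings of the comparator are open.

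| Reading | Support in the article | Motivation score available? | Does the claim hold? |
|---|---|---|---|
| The study's own controls | Quantitative data labels the comparator No IPS, as Sample size and power labels the 20 controls | Yes | No. Motivation can be balanced, other unmeasured factors cannot. With 20 candidates for 20 places and everyone kept, 1:1 matching leaves the group composition unchanged |
| A separate sample | Reconviction analysis sets a matched sample against the study participants | Not if it is built from records | No. The promise to control for motivation in all comparisons cannot be met |

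The claim fails on both readings; only the reason differs.

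**3. How large could the bias be?** The article gives no figure, so this is an illustration. Assumptions: no true IPS effect; log-odds of reoffending = −0.2 − 0.7U, where U is an unmeasured factor with SD 1, so the odds ratio is exp(−0.7) ≈ 0.50 per SD; U is higher by g = 0.5 or 0.8 SD in the IPS group.

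The average risk is approximately expit[(−0.2 − 0.7g)/√(1 + 0.346 × 0.49)], with denominator 1.0815:

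- g = 0: expit(−0.185) = 0.454
- g = 0.5: expit(−0.509) = 0.376, a difference of −0.078
- g = 0.8: expit(−0.703) = 0.331, a difference of −0.123

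A simulation of 2,000 runs per setting used logistic propensity matching, 1:1 without replacement, on four measured covariates each shifted by 0.4 SD:

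| Pool | g | Mean difference in U after matching | False reoffending difference |
|---|---|---|---|
| 20 | 0 | 0.00 | 0.00 |
| 20 | 0.5 | 0.51 | −0.077 |
| 20 | 0.8 | 0.81 | −0.122 |
| 200 | 0 | 0.00 | 0.00 |
| 200 | 0.5 | 0.50 | −0.078 |
| 200 | 0.8 | 0.81 | −0.120 |

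Matching leaves the unmeasured difference as it was, and a tenfold larger pool does not change that. U was independent of the measured covariates. To the extent that a real factor is correlated with them, matching would remove part of the bias.

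**4. How precise is the comparison?** Half-width = 1.96 × √[p(1 − p)(1/20 + 1/20)], with an assumed common reoffending rate p:

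- p = 0.30: 0.284
- p = 0.45: 0.308
- p = 0.60: 0.304

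The interval is therefore about ±28 to ±31 points. It covers sampling error only, not the bias in step 3.

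**The case against.** The strongest reply is that one overstated verb is being made to carry too much. The same section calls the counterfactual an estimate. The article admits the lack of randomisation, says the sample was set by time and resources, treats reoffending as secondary, and brings interviews and area crime rates into the interpretation. If the comparators are the study's own controls, motivation is measured and the article promises to adjust for it. Matching ratio, balance tables and interval reporting are usually left to an analysis plan.

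Much of this stands. Three stronger readings that a reader might infer are not supported:

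- *That the comparators come from police records and so have no motivation score.* The article names police data for the reoffending of those on IPS. It does not say where the comparators come from.
- *That the matching pool is too small to yield enough pairs.* The article gives the size of the matched sample, not of the pool. A matched sample of similar size is also what 1:1 matching from a large pool would produce.
- *That chance imbalance at 20 versus 20 discredits the matching.* Such imbalance would arise equally under randomisation, and the confidence interval allows for it.

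The reply does not rescue the sentence itself. Calling the counterfactual an estimate does not qualify a guarantee given two sentences later. Adjusting for motivation, where possible, deals with one confounder. This is an affirmative statement about what the analysis shows, not a detail left to another document.

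**Conclusion.** The point holds as a matter of wording and inference. The article claims that matching makes IPS the only major difference and so isolates its effect. Propensity matching cannot do this in a self-selected sample, and the promise to control for motivation reaches this comparison on only one of two possible readings of the comparator.

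This conclusion follows from the method and the stated design and needs no assumed figure. The sizes do rest on assumptions: a false difference of about 8 to 12 points depends on the confounder strength chosen, and an interval of ±28 to ±31 points depends on assumed reoffending of 30 to 60%. Because that bias is less than half the interval's half-width (12/28 ≈ 0.43), the likelier harm is over-reading the point estimate, not a spurious significant result.

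A reader might go further and infer that the matched comparison is worthless or that the design needs a larger comparator group. The article does not support either. A matched comparison labelled as an association is still informative, and a larger group would narrow the interval without removing unmeasured confounding. The point affects a secondary outcome and one listed research question, not the primary employment outcome.

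**What to change.** 1. Replace the sentence under Quantitative data with: *matching aims to balance the measured factors; unmeasured differences, including motivation where it is not available, may remain*. Change the stated aim of isolating the effect of IPS to match.
2. Report the difference in reoffending with a 95% confidence interval, as an association and not as an isolated IPS effect.
3. Show standardised differences on the matching factors after matching, so that readers can see what balance was achieved.
4. Reconcile Reconviction analysis with Quantitative data on who the comparators are. If they are the study's own controls, say so and include the motivation score in the propensity model. If they are a separate sample without that score, except this comparison from the promise to control for motivation throughout.

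The cost is a few sentences and one balance table, with no extra participants. If motivation is added, the propensity model carries one more variable with only about 40 people. The price is a more modest conclusion for research question 5.

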### Ethics and consent

Ethical approval for this study has been obtained from the National Health Service (NHS) Health Research Authority, reference number 15/NE/0049, and the NOMS ethics committee.

As this study will generate sensitive and personal data consideration of ethics and participant confidence is essential. Interviews will all be conducted in a sensitive manner. During interviews the participants’ verbal and non-verbal behaviour will be monitored to ensure that they are comfortable and able to continue. Participation is completely voluntary and participants may refuse to complete the study at any time or refuse to answer any of the questions for any reasons. Should the researcher feel that an individual is unstable, distressed and/or experiencing difficulties, or presents suicidal ideation, the interview will be stopped and the appropriate professionals contacted.

The researcher will also ensure that all activities and analyses are conducted to the highest ethical standards, adhering to relevant guidance. Participation in the research will be entirely voluntary and on the basis of written informed consent. Written informed consent for participation in the study will be obtained from each participant. Information sheets will also be administered to all those who may be present during observations with employment personnel in order to allow the individual (s) to opt out. Written informed consent will be obtained for participation prior to each interview and set of questionnaires administered. Information sheets and consent forms will be jargon free and created to account for diverse levels of literacy: Easy Read, for those that require such a format.

The information sheet and consent form will also ask consent for access to medical and criminal client information for the purpose of the research only. No promises of employment will be made to participants, which will also be made clear on the information sheet. Participants are not dependent on the relationship with the researcher and consequently their help to find work, if they are receiving any, will not change at any point should they withdraw or when the study ends.

Financial payments will be offered to participants for their time throughout the study. The exact details regarding how payments will be provided and when will be indicated on a separate form. This will be administered to participants when they have decided that they would like to take part in the study.

## Discussion

The study will be carried out across a wide geographical area. A total of eight sites, seven prisons and one probation area are eligible to provide referrals to the study, including both people who do and do not want help to find competitive employment via the IPS service. This will therefore involve conducting research within the demands of a criminal justice setting, with a population many of whom have chaotic lifestyles.

## Abbreviations

MoJ: Ministry of Justice
SMI: Severe Mental Illness
CJS: Criminal Justice System
IPS: Individual Placement and Support
IOM: Integrated Offender Management
NPS: National Probation Service
HMPS: Her Majesty’s Prison Service
NOMS: National Offender Management Service
PNC: Police National Computer
TAG: Threshold Assessment Grid
GHQ: General Health Questionnaire
BSI: Brief Symptom Inventory
MANSA: Manchester Short Assessment of Quality of Life
MTW: Motivation and Readiness to Work
SNA: Social Network Analysis
RE: Realistic Evaluation
CMOs: Contexts, Mechanisms and Outcomes
NHS: National Health Service
IPS-25: IPS Fidelity Scale
PSM: Propensity Scored Matching
UoN: University of Nottingham
US: United States
UK: United Kingdom
SPSS: Statistical Package for the Social Science
